**Methods/design:**

Elderly (≥70 years of age) patients admitted to the Royal Melbourne Hospital with delirium, and not requiring surgery, will be identified from the current practice of the investigators and through referral by other general medical unit staff. To facilitate this, other staff will be briefed on the project by investigators. Patients will be recruited with suitable informed and documented consent (person responsible) by the study investigators. They will receive orally either 5 mg melatonin (18 patients) or placebo (18 patients) nightly for 5 nights (or until discharged).

During treatment, participants will be assessed by study staff using a validated scale of delirium severity (the Memorial Delirium Assessment Scale), and a validated measure of delirium state (Confusion Assessment Method) to determine if melatonin decreases the severity or the duration of delirium. Assessment will continue for a further two days after treatment has ceased, to determine if the treatment causes persisting abatement of symptoms, and to assess for adverse events.

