### Study population and recruitment

During multidisciplinary meetings and the day-to-day duties of investigators, potential patients will be considered for inclusion. Patients with a diagnosis of delirium via the CAM and who are 70 years or older as general medical inpatients will be screened according to exclusion criteria. These exclusion criteria include solely hypoactive delirium (MDAS question 9), planned surgery, the inability to speak or understand English, severe sensory impairment or dysphasia, an expected prognosis or discharge of less than 7 days, severe hepatic failure (defined as Bilirubin ≥2.5 times upper limit of normal; alkaline phosphatase, aspartate transaminase and/or alanine transaminase > 3 times upper limit of normal), a markedly non-therapeutic INR (<1 or >4), use of melatonin or melatonin receptor agonist in the preceding 14 days, active seizure disorder (a seizure in the last month, or a seizure disorder not on anticonvulsants), and concomitant cimetidine use. As melatonin is a sedative medication, it’s clinically inappropriate to provide this to patients who have an exclusively hypoactive delirium as this may exacerbate the decreased conscious state. Also, as per Balan et al. [3], an exclusively hypoactive delirium may be associated with an elevated melatonin level. Patients who have surgery planned during the study period are to be excluded as surgery and anaesthesia are independent risk factors for delirium and would act as intra-intervention confounders.

Given patients with delirium are unable to provide informed consent, consent will be obtained by the person responsible for surrogate decision making and documented on clear consent forms. The surrogate decision maker retains the capacity to withdraw the patient from the trial at any time. If during the course of the trial the patient regains capacity due to the resolution of their delirium, a separate informed consent will be obtained should the patient wish to continue; if they do not, they will be withdrawn from the trial.

The Melbourne Health Human Research and Ethics Committee has evaluated and approved this trial.

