### Data collection

Baseline demographic data and current medication use (including as needed [PRN]) medications will be recorded. Following enrolment, patients will be visited by trained and qualified research staff every day to collect data and assess safety.

Delirium will be diagnosed using the Confusion Assessment Method (CAM) [12], as the primary outcome variable. This is a widely used instrument for the detection of delirium in the acute hospital setting. It has a sensitivity of 94–100 % and a specificity of 90–95 % and generates a DSM IV diagnosis of delirium. Duration of delirium will be recorded in days and delirium considered to have ceased the day of the last visit at which the participant was positive on CAM.

Delirium severity will be measured by the Memorial Delirium Assessment Scale (MDAS) [13], a validated scale suitable for use by both skilled clinical and trained observers, with good internal consistency and inter-rater reliability. The maximum MDAS score will be used as a measure of severity.

Comorbidity will be measured by the Charlson scale (Charlson Comorbidity Index, CMI) [14] from the history, patient, and/or surrogate; pre-morbid function will be measured using the Katz Activities of Daily Living (ADL) [15] index score from their condition two weeks prior to admission; depression will be measured using the GDS-15 item scale [16]; cognition will be measured by the mini-mental state examination (MMSE) [17].

Premorbid cognitive impairment will be determined both from chart review for a diagnosis of dementia or other cause of chronic cognitive impairment by a specialist neurologist, psychiatrist, or geriatrician, and the administration of the Informant Questionnaire for Cognitive Impairment or Dementia in the Elderly short form (IQCODE-sf) [18]. The IQCODE-sf will be completed with the assistance of primary caregivers.

Motor subtype of delirium does not have a validated scale and will be assessed by clinical judgement of the investigators.

Use of rescue medication will be determined from chart review and recorded by medication and average daily dose since last visit, and will be sub-stratified as required into groupings of those with significant anticholinergic activity, opioids, antipsychotics, and benzodiazepines.

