### Power analysis

The primary endpoint is a decrease in MDAS score from the baseline to the average score across days 1–5 of treatment. As a pilot trial, one of the feasibility objectives is to obtain the standard deviation for the primary outcome measure in order to allow a power calculation to be performed to assist with the development of an appropriately powered trial to test the relevant hypotheses. As such, no true power calculation can be calculated.

However, a trial of the prophylactic use of melatonin in a Canadian hospital [7] yielded entry data of an MDAS score of 11.4 with a standard deviation (SD) of 3.0. A clinically significant change on the MDAS (highest possible score of 30, lowest of 0, positively correlated with severity) of 3 points at 80 % power and a significance level of 5 % suggests 16 patients per arm. At a 10 % dropout rate and rounding up, the groups should be of 18 patients each.

It should be noted that these figures cannot be used to precisely calculate power, as they use MDAS score at entry into the trial (not during treatment), and the population is significantly different with an average length of stay of 14 days (around twice that of similar patients at RMH). While these results provide some guidance that a trial is possible and relevant group size and power achievable, a pilot is still required to confirm the exact numbers needed.

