### Statistics

Data will be collected for each patient on a daily basis, up to 7 days following recruitment. The primary and secondary outcome measures will be compared using standard statistical methodology. For continuous variables, results will be compared using a Students’ t-test with significance set to 0.05 if they are normally distributed, else a Mann-Whitney or other non-parametric test will be utilised. Control and treatment group homogeneity will be tested with Chi-square statistics. For discrete outcomes, results will be tested using a Chi-square test. Risk ratios will be employed where appropriate. The Hausman specification test will be used to determine whether the data should be analysed using either fixed or random effects, though it is expected that a random and fixed (mixed) effects model will be required.

Extensions to the statistical methods above may be required depending on what is found once the data is collected and the analysis is begun.

Missing data will be accounted for using the last observation carried forward method, and all data will be analysed according to the intention-to-treat principle primarily (and per-protocol analysis secondarily).

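### Delirium duration is dated to the last CAM-positive visit without an observed negative CAM, so participants who leave while still positive are scored as recovered, and the plan does not say whether LOCF overrides this

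*Protocol article*

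**What the plan says.** Duration of delirium is a secondary research question, and the abstract says the trial will determine whether melatonin shortens it. The Data collection section fixes how it is scored: "delirium considered to have ceased the day of the last visit at which the participant was positive on CAM". It does not require a later negative CAM, and it does not mention participants who leave early, die or remain delirious when follow-up ends.

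The Statistics section sets the window and the missing-data rule: "Data will be collected for each patient on a daily basis, up to 7 days following recruitment", and "Missing data will be accounted for using the last observation carried forward method". No outcome is exempted from carrying forward.

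Early exit is foreseen. Treatment in the abstract runs "nightly for 5 nights (or until discharged", and under Study population and recruitment "The surrogate decision maker retains the capacity to withdraw the patient from the trial at any time". The Power analysis allows for 10% dropout. Patients with "an expected prognosis or discharge of less than 7 days" are excluded, which limits early exit. The Power analysis also describes the comparison population as having "an average length of stay of 14 days (around twice that of similar patients at RMH", which puts the local average stay at about 14 / 2 = 7 days, so the exclusion cannot be expected to remove early discharge altogether.

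**The concern.** A duration is complete only when its end has been seen. Under the stated rule, a participant last seen CAM-positive on day 2 receives the same 2 days as one who was positive on day 2 and negative from day 3 onward. The first is a censored observation, the second a recovery.

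The rule thus shortens recorded delirium most for those observed least. If more participants in one arm leave or die while delirious, that arm appears to recover faster. This bears on a stated secondary question, in a pilot meant to guide a larger trial. The unexempted LOCF rule adds a second, quite different score for the same participant, and the text leaves the choice open.

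**Working it through.** **The plan's own figures.** None is given for duration. The only sample-size figure concerns the MDAS: the Canadian trial "yielded entry data of an MDAS score of 11.4 with a standard deviation (SD) of 3.0", and the target change is 3 points. n = 2 × (1.96 + 0.84)² × (3/3)² = 15.7, so 16 per arm, and 16 / 0.9 = 17.8, so 18. Both reproduce, and neither depends on the duration rule. The 10% dropout is the only exit figure in the document.

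**The two rules on single participants** (days 1 to 7):

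| CAM sequence | Data collection rule | LOCF first, then the rule |
|---|---|---|
| Positive days 1–2, then gone | 2 | 7 |
| Positive days 1–2, negative day 3, then gone | 2 | 2 |
| Positive to day 3, day 4 missed, negative from day 5 | 3 | 4 |
| Positive days 1–7 | 7 | 7 |

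The rules differ for those who leave CAM-positive and for a visit missed after a positive one. They agree for those who leave CAM-negative and for those positive throughout.

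**Size in group means.** My assumptions: the same true duration in both arms, median 5 days, constant daily chance of recovery; constant daily chance of leaving, unrelated to recovery; everyone CAM-positive on day 1.

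- s = daily probability of remaining delirious = 0.5^(1/5) = 0.8706.
- r = daily probability of staying in the study; total exit = 1 − r⁷.
- Mean under the Data collection rule: M = Σ (s·r)^(k−1) for k = 1 to 7 = [1 − (s·r)⁷] / (1 − s·r).
- Mean with LOCF applied first: L = 7 − [(1 − s)·r / (1 − s·r)] × (7 − M).
- Correct mean truncated at day 7: M with r = 1, that is (1 − 0.379) / 0.1294 = 4.80 days.

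Example at 10% total exit: r = 0.9^(1/7) = 0.9851, s·r = 0.8576, M = (1 − 0.341) / 0.1424 = 4.63, L = 7 − 0.895 × 2.374 = 4.88.

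| Total exit | r | M (stated rule) | L (LOCF) |
|---|---|---|---|
| 0% | 1 | 4.798 | 4.798 |
| 5% | 0.9927 | 4.713 | 4.836 |
| 10% | 0.9851 | 4.626 | 4.875 |
| 15% | 0.9771 | 4.537 | 4.915 |
| 19% (3% a day) | 0.97 | 4.460 | 4.950 |
| 59% (12% a day) | 0.88 | 3.613 | 5.351 |

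- 10% exit in both arms: each mean is short by 4.798 − 4.626 = 0.17, about 0.2 day. There is no gap between arms.
- 5% versus 15% (averaging the planned 10%): false gap 4.713 − 4.537 = 0.176 day, favouring the arm with more exits. Under LOCF the gap is 4.915 − 4.836 = 0.08 day the other way.
- 19% versus 59%: false gap 4.460 − 3.613 = 0.85 day; under LOCF 0.40 day the other way.
- Assumed medians of 3 to 7 days give, from the same formula, 0.12 to 0.21 day at 5% versus 15%.

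**Against sampling error.** The SD of the truncated duration in this model is about 2.3 days. With 18 per arm the standard error of the difference is 2.3 × √(2/18) = 0.77 day, more than four times the 0.176-day gap.

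**Still delirious after day 7.** With no early exit, s⁷ = 0.379: about 38% would remain delirious beyond day 7 yet be recorded as ceased on day 7 (20% to 50% for medians of 3 to 7 days).

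**The case against.** The strongest defence has four parts.

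- **Exit is limited.** Short expected stays are excluded, planned dropout is 10%, and the trial is blinded. At such rates the distortion is small beside the sampling error. This stands for the size of the bias, though the local stay of about 7 days means discharge could exceed 10%. It does not make the rule right.
- **A score of 7 for someone delirious throughout is legitimate** as duration within a 7-day window. With no early exit the rule returns exactly the truncated mean of 4.80. A reader might infer that persistence at day 7 biases the comparison; it does not. What remains is that a censored duration is called ceased.
- **The two rules need not contradict each other.** The duration rule speaks of a visit, and an imputed day is not a visit. On that reading it governs duration and LOCF fills only daily scores. That is reasonable, but the article does not say so. The defect is unstated precedence, not a proven contradiction.
- **The listed CAM endpoint may mean daily status.** A reader might take presence or absence over days 1–7 as any delirium in that window, which would be nearly universal because entry requires a positive CAM. Since the CAM is recorded daily and a mixed model is expected, daily status is at least as natural. The wording needs settling; it is not shown to be useless.

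It is also tempting to say that everyone who is discharged, withdrawn or dies is counted as recovered that day. The text does not support this. Those who leave CAM-negative are dated correctly, including those who regain capacity as delirium resolves and then decline to continue.

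**Conclusion.** The rule is stated in the article and fixed badly; it is not a detail left to an unseen analysis plan. It turns censored durations into completed ones for participants CAM-positive at their last visit, and nothing says whether LOCF replaces that score with one biased in the opposite direction.

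The likely effect is modest: about 0.2 day of shortening at the planned 10% exit and no between-arm gap if exit is equal. The false gap is just under 0.18 day at 5% versus 15%. The 0.85-day figure requires most of one arm to leave, and no figure in the document supports that. All of these rest on an assumed median of 5 days and on exit unrelated to recovery.

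This is a correction to a secondary outcome. The primary endpoint in the End points and Power analysis sections is the change in MDAS, which the duration rule does not touch. (The Data collection section describes the CAM as the primary outcome; I follow the End points section.)

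**What to change.** - Define recovery as the first observed CAM-negative visit not followed by a positive one through day 7.
- Censor participants who are CAM-positive at last contact or at day 7. Treat death as a competing event, not as recovery.
- Compare arms on time to resolution, by Kaplan–Meier and log-rank, or by cumulative incidence where deaths occur.
- State that LOCF does not apply to the CAM or to duration.
- State that the secondary CAM endpoint means presence or absence on each day, not any delirium during days 1–7.

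Censoring at discharge assumes that discharge is unrelated to recovery, which may not hold. Add a sensitivity analysis that counts participants discharged CAM-positive as unresolved to day 7.

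The cost is the rewording of one definition and one endpoint, plus one sentence on missing data. The CAM is already scheduled at entry and daily through day 7, so no new data are needed. With complete daily visits, dating recovery to the first negative visit adds one day to each observed recovery time in both arms and does not affect the comparison.

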### Delirium treatment

All patients will receive care based on current practice at the Royal Melbourne Hospital, which is based on standard procedures including behavioural management, reorientation, and pharmacotherapy when indicated. If a patient is already on antipsychotic medication, this will continue throughout the trial.

### Power analysis

The primary endpoint is a decrease in MDAS score from the baseline to the average score across days 1–5 of treatment. As a pilot trial, one of the feasibility objectives is to obtain the standard deviation for the primary outcome measure in order to allow a power calculation to be performed to assist with the development of an appropriately powered trial to test the relevant hypotheses. As such, no true power calculation can be calculated.

However, a trial of the prophylactic use of melatonin in a Canadian hospital [7] yielded entry data of an MDAS score of 11.4 with a standard deviation (SD) of 3.0. A clinically significant change on the MDAS (highest possible score of 30, lowest of 0, positively correlated with severity) of 3 points at 80 % power and a significance level of 5 % suggests 16 patients per arm. At a 10 % dropout rate and rounding up, the groups should be of 18 patients each.

It should be noted that these figures cannot be used to precisely calculate power, as they use MDAS score at entry into the trial (not during treatment), and the population is significantly different with an average length of stay of 14 days (around twice that of similar patients at RMH). While these results provide some guidance that a trial is possible and relevant group size and power achievable, a pilot is still required to confirm the exact numbers needed.

### Statistics

Data will be collected for each patient on a daily basis, up to 7 days following recruitment. The primary and secondary outcome measures will be compared using standard statistical methodology. For continuous variables, results will be compared using a Students’ t-test with significance set to 0.05 if they are normally distributed, else a Mann-Whitney or other non-parametric test will be utilised. Control and treatment group homogeneity will be tested with Chi-square statistics. For discrete outcomes, results will be tested using a Chi-square test. Risk ratios will be employed where appropriate. The Hausman specification test will be used to determine whether the data should be analysed using either fixed or random effects, though it is expected that a random and fixed (mixed) effects model will be required.

Extensions to the statistical methods above may be required depending on what is found once the data is collected and the analysis is begun.

Missing data will be accounted for using the last observation carried forward method, and all data will be analysed according to the intention-to-treat principle primarily (and per-protocol analysis secondarily).

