### End points

#### Primary

Change in MDAS score from baseline to average over days 1–5

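### The primary MDAS comparison has no single fixed analysis and no baseline covariate; adjusting for entry MDAS is in general at least as precise and costs almost nothing

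*Protocol article*

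**What the plan says.** The primary end point in the Protocol article is "Change in MDAS score from baseline to average over days 1–5" (End points, Primary). Table 1 schedules the MDAS at entry and on every later visit, so the baseline score is already collected.

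The Statistics section covers all outcomes together: "The primary and secondary outcome measures will be compared using standard statistical methodology". For continuous variables that means a Student's "t-test with significance set to 0.05 if they are normally distributed, else a Mann-Whitney or other non-parametric test will be utilised". No baseline covariate and no criterion for normality are given.

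Two further sentences widen the choice. The section proposes a Hausman test to decide between fixed and random effects and adds that "it is expected that a random and fixed (mixed) effects model will be required". This model is attached to no outcome, has no stated baseline term and is not ranked against the t-test. The section then says: "Extensions to the statistical methods above may be required depending on what is found once the data is collected and the analysis is begun".

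Under Power analysis the trial is described as a pilot, and "one of the feasibility objectives is to obtain the standard deviation for the primary outcome measure".

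**The concern.** There are two separate issues.

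**Precision.** A change score subtracts one entry score with a weight of exactly 1. The weight that minimises variance is the regression slope of the day 1–5 mean on baseline. For a fluctuating condition, with one baseline day set against a five-day mean, that slope may be well below 1. The subtraction then adds noise, and in any one trial it over-corrects a chance imbalance at baseline.

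**What is being estimated.** A t-test reports a mean difference in MDAS points; a Mann-Whitney test compares ranks. If the distribution seen in the data selects the test, it also selects the effect measure. The open wording on other non-parametric tests, the unattached mixed model and the allowance for later extensions leave the choice wider still.

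At stake are the width of the interval around the treatment effect in a trial of 18 per arm, and a clear definition of the result to be carried into the definitive trial.

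**Working it through.** **1. The plan's own figure.** Inputs from Power analysis: an earlier trial "yielded entry data of an MDAS score of 11.4 with a standard deviation (SD) of 3.0", and a change "of 3 points at 80 % power and a significance level of 5 % suggests 16 patients per arm". Sidedness is not stated; two-sided is assumed.

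n = 2 × (1.960 + 0.842)² × 3.0² / 3² = 15.7, so 16 per arm; 16 / 0.9 = 17.8, so 18. Both stated figures reproduce. The SD of 3.0 is an entry SD. For a change to a single later score with equal SDs, the SD is 3.0 × √(2(1 − r)), which equals 3.0 only at r = 0.5.

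**2. General relation.** Let β be the slope of the day 1–5 mean on baseline. Then

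Var(change) = Var(ANCOVA residual) + (1 − β)² × Var(baseline).

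The extra term is never negative and vanishes only at β = 1. ANCOVA pays one degree of freedom for estimating β.

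**3. Size for a five-day mean.** Assumptions, not in the documents: equal SDs on all days and the same correlation r between any two days. In units of the daily variance, Var(day 1–5 mean) = (1 + 4r)/5 and β = r, so

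- Var(change) = 1 + (1 + 4r)/5 − 2r = 1.2(1 − r)
- Var(ANCOVA residual) = (1 + 4r)/5 − r²

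| r | change | ANCOVA | ratio |
|---|---|---|---|
| 0.3 | 0.84 | 0.35 | 2.40 |
| 0.5 | 0.60 | 0.35 | 1.71 |
| 0.7 | 0.36 | 0.27 | 1.33 |
| 0.8 | 0.24 | 0.20 | 1.20 |
| 0.9 | 0.12 | 0.11 | 1.09 |

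**4. On the MDAS scale.** Take r = 0.5, daily SD 3.0 and 16 per arm. The SDs are 3.0 × √0.60 = 2.32 and 3.0 × √0.35 = 1.77. The 95% CI half-widths, t × SD × √(2/16), are 1.68 (30 df) and 1.28 (29 df) points. Multiplying the ANCOVA variance by 1 + 1/28 for estimating the slope raises 1.28 to about 1.31.

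**5. If the spread differs after baseline.** Let each follow-up SD be k times the baseline SD (k is illustrative).

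- Single follow-up score: ratio = (1 + k² − 2kr) / (k²(1 − r²)). At k = 1 this is 2/(1 + r): 1.54, 1.33 and 1.18 at r = 0.3, 0.5 and 0.7. At k = 1.25 and r = 0.5 it is 1.3125/1.1719 = 1.12; at r = 0.7 it is 1.02. At k = 1.5 these become 1.04 and 1.00.
- Five-day mean: ratio = [1 + k²(1 + 4r)/5 − 2kr] / [k²((1 + 4r)/5 − r²)]. At k = 1.25 it is 0.6875/0.5469 = 1.26 at r = 0.5 and 0.4375/0.4219 = 1.04 at r = 0.7.

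**6. Chance imbalance.** With 16 per arm the SD of the baseline difference is 3.0 × √(2/16) = 1.06 points. Given a difference of that size, the change-score estimate shifts by (1 − β) × 1.06, or 0.53 points at β = 0.5, in the opposite direction. Over all randomisations the shift averages zero.

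**7. Data-chosen test.** Simulation under no effect: 16 per arm, 8,000 runs, Shapiro-Wilk at 0.05 as an assumed normality check. The rule of t-test if passed, Mann-Whitney if failed, rejected in 0.050 (normal), 0.053 (lognormal) and 0.054 (exponential) of runs; simulation standard error about 0.0024. Taking the smaller of the two p-values gave 0.057 to 0.063.

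**The case against.** There are good arguments in favour of the plan, and several of them stand.

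- *The section also foresees a mixed model.* True, so it would be wrong to say flatly that an unadjusted t-test is the only planned analysis. But with no outcome, no baseline term and no stated priority, that sentence does not supply the adjustment. It adds a second choice to be made on the data.
- *A change score does use baseline.* Correct. A reader might infer that the entry score is wasted or the estimate biased. Neither follows: baseline enters with slope 1, and the t-test is valid and unbiased under randomisation. The shift in step 6 is conditional on the imbalance that happens to occur.
- *The pilot still gets its SD.* Correct. One might infer that a rank test deprives the definitive trial of its planning figure. The SD of change is what Power analysis asks for, and it can be reported whichever test gives the p-value. The residual SD and the baseline correlation can be computed from the same daily data.
- *Choosing the test by a normality check does little harm to the error rate.* Correct on the simulation. What remains is the unfixed effect measure.
- *The size of the gain is assumed.* Correct. No correlation is given, the SD of 3.0 comes from another trial's entry scores, and Power analysis itself warns against using it for a precise calculation. Under the five-day model of step 3, the planned change-score t-test at 16 per arm would have 85%, 94% and 99.5% power for 3 points at r = 0.3, 0.5 and 0.7.
- *This is a pilot described in a condensed article.* That softens the consequence. The article nonetheless commits to a method and a 0.05 threshold for the primary outcome, so this is a stated choice and not a detail left to an analysis plan.

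**Conclusion.** The point holds as a recommendation on precision and pre-specification. It does not show an invalid analysis.

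The direction is firm: apart from one degree of freedom, the change-score comparison cannot be more precise than a baseline-adjusted one. The size is not firm. With equal daily SDs and equal correlation r of 0.3 to 0.7, the change-score variance is about 2.4 to 1.3 times the ANCOVA variance. The ratio approaches 1 if r is high, or if scores spread out after baseline so that the slope is near 1.

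Separately, the section leaves the choice between t-test, rank test and mixed model to the data. The cost is an undefined effect measure; type I error stays close to 0.05. The documents do not support claims of bias, of a discarded baseline, of a materially inflated false-positive rate or of a lost planning SD.

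**What to change.** In the Statistics section, name one primary analysis. For example: mean MDAS over days 1–5 is compared between arms by ANCOVA with baseline MDAS as covariate (or by a mixed model of daily MDAS with baseline as covariate), reporting the adjusted mean difference with its 95% CI. If the mixed model is preferred, say that it is primary and drop the Hausman step for this outcome.

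Keep a rank or permutation test as a sensitivity analysis, done whatever any normality check shows.

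For the definitive trial, report the SD of change, the residual SD and the correlation between baseline and the day 1–5 mean.

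The cost is a few sentences of text and one degree of freedom. No new data are needed.

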### Randomisation & blinding

After enrolment, patients will be randomised into treatment groups by drawing a sealed, opaque envelope from a box containing an allocation code (randomised by an unrelated statistician). The box contains equal numbers of allocation codes to a total of the expected number of participants. The envelope and code are discarded after being drawn. The envelopes will be in permuted blocks of 4 (2 placebo 2 active).

The results of this randomisation are not known to any of the investigators or intervention administration staff. A separate code interpretation sheet is kept locked in the trial pharmacy, where after the completion of data collection the allocation codes will be matched to provide the requisite placebo vs intervention information.

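### The Hausman rule for choosing fixed or random effects does not suit a parallel-group trial: with patient fixed effects the arm main effect drops out, and the governing primary analysis is never named

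*Protocol article*

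**What the plan says.** All references are to the protocol article.

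- **Endpoint (End points, Primary).** "Change in MDAS score from baseline to average over days 1–5". This is one number per patient, and it uses the day 0 score.
- **Design (Randomisation & blinding).** Allocation is individual: "patients will be randomised into treatment groups by drawing a sealed, opaque envelope". The arms are parallel, in blocks of four with two active and two placebo.
- **Data (Statistics).** "Data will be collected for each patient on a daily basis, up to 7 days following recruitment". Table 1 lists MDAS at entry and at every later visit.
- **First analysis named (Statistics).** For continuous variables, "results will be compared using a Students’ t-test with significance set to 0.05 if they are normally distributed", with Mann-Whitney or another non-parametric test otherwise.
- **Second analysis named (Statistics).** "The Hausman specification test will be used to determine whether the data should be analysed using either fixed or random effects", followed by the forecast "though it is expected that a random and fixed (mixed) effects model will be required".
- **Room for change (Statistics).** "Extensions to the statistical methods above may be required depending on what is found once the data is collected and the analysis is begun".

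The section does not say which unit carries the effects, how treatment enters the model, whether day 0 is a response or a covariate, or which outcome the model serves.

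**The concern.** The Hausman test asks whether unit-level effects are correlated with the regressors. If they appear to be, fixed effects are chosen. In a parallel-group trial the regressor of interest is arm, which never changes within a patient. Patient fixed effects therefore remove the arm main effect, and the test is silent about arm because only one of the two models estimates it.

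The rule is thus badly matched to the design in two ways. One of its outcomes leads to a model without the parameter that the primary question needs, unless the model is laid out in a particular way that the article does not describe. And the question the test asks has already been answered for arm by randomisation.

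The section also gives the same continuous outcomes two routes, a two-sample test and a panel model chosen by the data, and does not say which one governs the primary endpoint. The clause on extensions leaves further choices open after analysis has begun. At stake is whether the primary MDAS result comes from one analysis fixed in advance.

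**Working it through.** **1. The plan's own figure.** Inputs from Power analysis: difference 3 points, SD 3.0, power 80 %, significance 5 % (two-sided assumed), dropout 10 %.

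n per arm = 2 × (1.960 + 0.842)² × (3.0/3)² = 15.7, so 16. With dropout, 16/0.90 = 17.8, so 18.

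Both figures reproduce. The layout is 36 patients, 18 per arm. Nothing below alters them.

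**2. Can arm be estimated with patient fixed effects?** I built the design matrix with 36 patient dummies and a dummy for each day after the first, then added treatment terms. A term is estimable only if it raises the rank.

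| Response rows | Patient + day | + arm | + arm × post-baseline | + arm × linear day |
|---|---|---|---|---|
| Days 1–5 | 36 + 4 = 40 | 40 | 40 | 41 |
| Days 1–7 | 36 + 6 = 42 | 42 | 42 | 43 |
| Days 0–5 | 36 + 5 = 41 | 41 | 42 | 42 |

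The arm main effect adds nothing in any layout, because the arm column is the sum of the dummies of the patients in that arm. Arm by linear day is estimable throughout, but it measures a difference in trend, not the average difference over days 1–5. Arm by post-baseline is estimable only when day 0 is a response row.

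**3. What that surviving term estimates.** In simulated complete data for days 0–5, the fixed-effects coefficient for arm by post-baseline was −2.088. The between-arm difference in the change from day 0 to the days 1–5 mean was also −2.088. The fixed-effects branch, laid out this way, returns the unadjusted change-score contrast.

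**4. What the Hausman statistic does here.** The statistic is H = (b_FE − b_RE)′ [V_FE − V_RE]⁻¹ (b_FE − b_RE), over the coefficients that both models estimate. Arm is not among them. I fitted both models to simulated complete panels with day terms, with and without arm-by-day terms, using a common error variance, in all three layouts. Coefficients and variances agreed to within 1e-13, which is rounding error. The statistic is then 0/0 and gives no decision. Carrying the last observation forward, as Statistics prescribes, fills later gaps and pushes the real data towards this balanced case.

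**5. Why adjust for baseline.** Assume, for illustration, that all daily scores have equal variance (set to 1) and equal pairwise correlation ρ. The document gives no ρ.

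- Variance of the days 1–5 mean: (1 + 4ρ)/5 = 0.2 + 0.8ρ.
- Change score: 0.2 + 0.8ρ + 1 − 2ρ = 1.2(1 − ρ).
- Baseline-adjusted: 0.2 + 0.8ρ − ρ² = (1 − ρ)(0.2 + ρ).
- Ratio, adjusted to change score: (0.2 + ρ)/1.2.

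The ratio is below 1 for every ρ below 1. Over an assumed range of ρ from 0.3 to 0.7 it runs from 0.5/1.2 = 0.42 to 0.9/1.2 = 0.75, ignoring the small cost of estimating the slope.

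**The case against.** The strongest reply is that the primary endpoint is already a single change score per patient, the section first names a t-test or Mann-Whitney for such outcomes, and the Hausman sentence is not tied to the primary outcome. The authors also expect a mixed model, which is the class of model one would recommend. Names of units, treatment terms and response rows commonly belong in a full protocol or analysis plan, which is not shown.

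Much of this stands. The patient as unit is an inference, and the missing model detail is no fault by itself. But the Hausman sentence is a stated rule. The expectation of a mixed model is a forecast and does not override a test that is to decide. Naming a t-test as well leaves two routes to the same outcome with no order between them.

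Three stronger readings are tempting, and the document does not support them.

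- A reader might infer that the fixed-effects branch leaves no route at all to a treatment effect. That is wrong: day 0 MDAS is collected, and an arm-by-post-baseline term with day 0 as a response recovers the primary contrast.
- A reader might infer that a 5 % test would send about one trial in 20 down that branch. That rate needs a well-defined statistic, and in the balanced layout it is 0/0. No covariate that would give the test content is specified.
- A reader might infer that the primary result necessarily depends on the test. The text does not say so; it leaves the matter open.

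Pilot status does not remove the point. The primary research question concerns efficacy on MDAS, tests are set at 0.05, and the trial is meant to supply the SD for a larger one.

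**Conclusion.** The point holds in a limited form. If the effects are patient effects, the fixed-effects branch cannot estimate the arm main effect from post-baseline days (rank 40 with and without arm for days 1–5; 42 and 42 for days 1–7). With day 0 as a response row it yields only the unadjusted change-score contrast. The Hausman test serves no purpose for the treatment comparison, because it cannot use the arm coefficient, because randomisation secures for arm what it checks, and because it is degenerate in a balanced panel with day and arm-by-day terms alone. The primary endpoint has no single named analysis.

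This rests on the patient being the unit, on complete or filled-in daily data for the degeneracy result, and on no within-patient covariates beyond those terms. The effect on the trial's result cannot be put as an error rate. The planned 18 per arm is unaffected. This should be corrected, but it is not fatal to the trial.

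**What to change.** Delete the Hausman sentence and name one primary analysis that adjusts for baseline MDAS. Either of these would do:

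- analysis of covariance on the days 1–5 mean MDAS, with arm and baseline MDAS; or
- a linear mixed model for daily MDAS on days 1–5 with arm, day, baseline MDAS and a random patient intercept, reporting the arm contrast averaged over days 1–5.

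Say that this analysis governs the primary endpoint and that any t-test or rank test of it is supportive. Replace the sentence on extensions with a rule such as: changes of method are documented before allocation codes are matched, and any made later are labelled exploratory.

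The cost is a few sentences. Baseline MDAS is already collected, and no visit, patient or sample-size figure changes.
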